### Inclusion and exclusion criteria

Every medical record created in the health centre for homeless people from the year 2006 until 2020 will be entered in the database and included in the analysis (N ≈ 3000). There are no other inclusion or exclusion criteria.

### Measures

Data will be extracted from medical records and was collected within routine medical care by medical doctors and health care personnel. Data was primarily collected for the purpose of medical care documentation in the health centre. However, a variety of health and social information can be obtained from the medical records. Generally, data can be divided in eight data sources. An overview of all data sources can be obtained from Table 1.

### Pretest and quality assurance

After creating a first database, a pretest was conducted to ensure a complete and fully operational data entry. The pretest included *N* = 55 medical records. Data was entered by two experienced research associates. Data entry was documented and conspicuous differences and needs for adjustment collected. Based on the pretest the database was revised and edited. The new database was again tested with *N* = 10 medical records. Further, minor changes where implemented, and the data base was finalised. Data will be entered by two trained medical students. For quality insurance, prior to the beginning of data entry, a training on the data base and data collection was conducted with the medical students. Further, a code book for data entry was developed. Regular supervisions and random controls of data entry will be taking place during the entire period of data entry.

### Statistical analysis

Total and cross-sectional sample characteristics will be presented in a descriptive analysis using Chi-Square Test, Mann-Whitney-U-Test or independent t-Test as appropriate to test (sub) group differences. The absolute standardised mean difference (ASMD) will be calculated to check the balancing of the characteristics. We consider ASMD< 0.1 as adequate balance between groups. The level of significance will be considered at 0.05. Further, statistical analyses might use finite mixture modelling – particularly latent class analysis – in order to distinguish different types of social and health conditions. We will conduct latent variable regression in order to identify sociodemographic and disease-related factors associated with decreasing health conditions.

By performing latent class analysis collinearity between indicator variables is not a problem, since these procedures are aimed precisely at such configurations and patterns. Latent class analysis explicitly assumes that manifest variables occur in common expressions. In contrast, the usual limitations of conventional regression models apply for exogenous covariates. To increase estimation accuracy, we aim at testing for collinearity between covariates using the following two different approaches. First, a correlation matrix of predictor variables will be calculated. Bivariate correlations larger 0.8 indicate collinearity. Second, we will compute coefficients of determination of each independent variable regressed on the remaining predictor variables to reveal collinear relationships involving more than two variables. Single coefficients of determination being larger than the overall model’s coefficient of determination indicate collinearity [51].

All statistical analyses will be performed using IBM SPSS statistics software (IBM SPSS Statistics for Windows, Version 25.0).

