### Aim of the present study

The main aim of the present study protocol is the description of the objectives, design, methodology and potential limitations of the GIG study. The objectives of the retrospective analysis can be summarised as the following: 1) comprehensive socio-demographic characterisation of patients and 2) detailed description and analysis of health status and medical history (including utilisation of social and medical services). Both are analysed cross-sectional and longitudinal. Evaluation of longitudinal data will include analysis of individual courses (intra-individually for patients with multiple measure points), as well as analysis of trends where cross sections are considered over time (inter-individual analysis). In line with the study design (retrospective analysis of medical records), research questions will be examined in an explorative manner, based on type and quality of data available from medical records (document analysis). Among others, we aim to address the following research questions:

#### Objective 1

*O1a: Characterise the sample by age, education, gender, migration background, insurance status, detention experience, type of accommodation.*

*O1b: How often is there a change in the homeless status over time? How does the socio-demographic structure change over time?*

#### Objective 2

*O2a: Which are the most frequent health problems homeless people face?*

*O2b: How is the health and social services utilisation among homeless people?*

*O2c: How often/long are patients receiving care in the health centre?*

*O2d: Is there a change in health or social challenges during the last years?*

*O2e: Is there a change in frequency of specific diseases over time?*

*O2f: Are there associations between extreme social conditions and the health status of individuals?*

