To sum up, homelessness has serious implications for the health of individuals and populations. Based on the findings of the present study we expect to gain a better understanding on the health situation of homeless people in Germany and draw implications for its improvement by adapting services to changes in population demographics and morbidities. In order to improve health care services for homeless people, the further development of multifarious and diverse approaches seem necessary [53]. Thus, we expect the results to reveal a wide range of implications. For example, in a study conducted by Kaduszkiewicz et al. [13] a variety of concrete suggestions such as improving state funding and the range of health services and providing intermediate care centres were discussed. In order to achieve a long-term improvement, we believe it is inevitable to include and examine social policy and structural factors that contribute to or result in homelessness [54].

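### No standardised or adjusted trend is stated for disease frequency (O2e), so a shift in patient mix could be read as a change in morbidity, or could hide one

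*Protocol article*

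**What the plan says.** The section on the aim of the study describes the trend analysis as an "analysis of trends where cross sections are considered over time (inter-individual analysis)". Two of its questions bear on this point. O2e asks "Is there a change in frequency of specific diseases over time", and O1b asks "How does the socio-demographic structure change over time".

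For methods, the Statistical analysis section states: "Total and cross-sectional sample characteristics will be presented in a descriptive analysis using Chi-Square Test, Mann-Whitney-U-Test or independent t-Test". It adds a balance check, "We consider ASMD< 0.1 as adequate balance between groups", and an alpha: "The level of significance will be considered at 0.05". The one planned model with covariates is introduced so: "We will conduct latent variable regression in order to identify sociodemographic and disease-related factors associated with decreasing health conditions". Calendar year or period is not named as a term in it.

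The Discussion lists the handling of time as a strength and there treats cross-sectional analysis and analysis of trends as the same thing. It also gives the intended use of the findings: "adapting services to changes in population demographics and morbidities".

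Table 1 shows that age, year of birth, sex and citizenship are extracted. Age, sex and citizenship are linked to O1a, O2d and O2f, and year of birth to O1a and O2d. None is linked to O2e.

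**The concern.** A disease frequency among the centre's patients can change for two reasons. Patients of a given age, sex and origin may have become more or less ill, or the centre may be seeing a different mix of patients. An unadjusted comparison of calendar periods returns the sum of the two.

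The article asks about both kinds of change and wants services adapted to both, but it names nothing that would separate them for O2e. An older intake could then be read as rising morbidity, and a real fall in morbidity could be masked by an older intake. This would be so even if every cross-section held only first-time patients.

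**Working it through.** The article gives no trend figure, prevalence or yearly patient mix, so there is no figure of its own to reproduce. The check below illustrates the mechanism.

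**Inputs from the article.** About 3000 records (Inclusion and exclusion criteria); alpha 0.05, taken as two-sided; ASMD limit 0.1 (Statistical analysis).

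**Assumed inputs.** Two periods of n = 1500 independent records each; a disease with prevalence 5% below age 40 and 20% from age 40, unchanged over time; a share s aged 40 or over that starts at 50%.

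**Formulas.**
- Crude frequency: p = 0.05 × (1 − s) + 0.20 × s.
- ASMD of the age share: |s₂ − s₁| / √{[s₁(1 − s₁) + s₂(1 − s₂)]/2}.
- Rejection probability: normal approximation for two proportions, Φ[(d − 1.96·SE₀)/SE₁] plus the small opposite tail. Here d = p₂ − p₁, SE₀ uses the pooled proportion and SE₁ the separate ones.

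**Share 50% to 65%.**
- p₁ = 0.025 + 0.100 = 0.125 and p₂ = 0.0175 + 0.130 = 0.1475, a relative rise of 18%.
- ASMD = 0.15/√[(0.25 + 0.2275)/2] = 0.31.
- SE₀ = √(2 × 0.13625 × 0.86375/1500) = 0.0125, and SE₁ is the same to four decimals.
- Rejection probability ≈ Φ(−0.16) = 43%.

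**The other cases, same formulas, n = 1500 per period.**

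| Prevalence in the two groups | Share of the higher-risk group | ASMD | Crude frequency | Crude test rejects |
|---|---|---|---|---|
| 5% / 20% | 50% to 70% | 0.42 | 12.5% to 15.5% (+24%) | 66% |
| 5% / 15% | 50% to 60% | 0.20 | 10.0% to 11.0% (+10%) | 14.5% |
| 5% / 20% | 50% to 55% | 0.10 | 12.5% to 13.25% (+6%) | 9% |
| 20% / 30% | 50% to 55% | 0.10 | 25.0% to 25.5% (+2%) | 6% |
| 10% / 40% | 50% to 55% | 0.10 | 25.0% to 26.5% (+6%) | 16% |

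In every row nothing changes within the groups, so a test of within-group change should reject in 5% of cases.

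**Does adjustment repair it?** A further assumed case has prevalences of 20% and 40%, a higher-risk share rising from 30% to 50% (ASMD 0.42), and crude frequency going from 26% to 30%. The formula gives 68% rejection for the crude test. In 2000 simulated data sets the crude chi-square rejected in 68% and a stratified Cochran-Mantel-Haenszel test in 4.6%.

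**Masking.** Suppose the share aged 40 or over rises from 50% to 65% while both prevalences fall by the factor 0.125/0.1475 = 0.847. The crude frequency then stays at 12.5%, and a 15% relative fall in each age group is invisible.

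**Smaller periods.** With about 200 records per period (3000 records over 15 calendar years), the 50% to 65% case gives 10% rejection and the 50% to 70% case 14%.

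**The case against.** A reader might infer that the plan tests disease trends with unadjusted tests and will therefore report a changing patient mix as changing morbidity. The article does not support that.

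- The sentence on the three tests concerns sample characteristics and subgroup differences. Its tie to O2e runs through the Discussion, which equates cross-sectional analysis with trends. No trend method is assigned to O2e by name, and a journal article may leave that detail to a fuller plan.
- Table 1 links age, sex and citizenship to O2d, so a demographic view of changing health challenges is foreseen there.
- The missing O2e link cannot show that adjustment is excluded, because the column is loose. Number of visits and duration of care are not linked to O2c, the question on how often and how long patients receive care.
- Read literally, O2e is answered by crude frequency. In the example the frequency does rise from 12.5% to 14.75%, and a significant crude test is a true finding about what the centre sees. Service planning needs that figure, so drawing conclusions from standardised figures alone would hide it.
- O1b will report demographic change alongside, and the work is declared exploratory.

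All of this stands, and it limits the point to what could happen. It does not remove it. The ASMD check would flag the larger shifts above, but the article does not say what then happens to the trend estimate. The latent variable regression names no calendar term. The exploratory label does not change what a crude trend can and cannot show.

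**Conclusion.** The concern holds as a gap in interpretation. It is not an error in how O2e is worded. As the article stands, nothing named in it separates a change in patient mix from a change in morbidity, although it expects that the first may occur and wants to act on both.

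The size is unknown from the document. Under the assumed prevalences and 1500 v 1500 records, false signals of within-group change run from about 6 to 16% at the plan's own ASMD limit to 43 to 66% when the share aged 40 or over rises by 15 to 20 percentage points. They are less frequent with single-year periods. These figures rest wholly on the assumed prevalences, shares and two-period split, and on treating records as independent. They show that the effect can matter, not that it will.

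**What to change.** For O2e, and for the disease part of O2d:

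1. Report crude yearly frequencies beside age-sex-standardised ones, with the pooled 2006–2020 patients as the standard. Alternatively, report a regression of disease presence on calendar year with age, sex and citizenship group as covariates. Citizenship needs a small number of predefined groups, since it is recorded from a list of 202 countries.
2. State the use of each: crude figures for service load, adjusted figures for any statement that morbidity changed.
3. Give the ASMD check a consequence: where it is 0.1 or more between periods for age, sex or citizenship group, the adjusted result carries the morbidity statement.
4. Add O2e to the age, sex and citizenship rows of Table 1.

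The cost is a little more analysis, with no new data collection. Records without age, sex or citizenship drop out of an adjusted trend that uses that variable. The Discussion says some records are incomplete, so these should be counted and reported by period.

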**1**	**Floating medical record**	General information	status of homelessness/ type of accommodation	own flat, hostel, sleeps at friends/ acquaintances, shelter, carrier housing, sleeping rough, other	O1a, O1b, O2d
			status of health insurance	not insured, insured (type of company)	O1a, O1b, O2d
			birthday	year of birth	O1a, O2d
			number of visits	in total	O1a, O1b, O2d
			number of medical consultations	–	O1a, O1b, O2d
			duration of care (date of first and last visit)	in years	O1a, O1b, O2d
			indications of debts	no, yes	O1a, O1b, O2d
		Utilization of health centre services	medical reason	need of primary care, eye specialist, dentist	O2b, O2c
			counselling	(at risk of) homelessness in need of psychologist, social worker, legal advice	O2b, O2c
			Other	food, new clothes, hairdresser, shower, other	O2b, O2c
		Medical history	diagnosis and provided treatment, medication, further recommendations	date of issue, 3-digit ICD-10-GM code*, prescribed medication by ATC code**	O2a, O2b, O2c, O2d, O2e, O2f
**2**	**Social and medical anamnesis**	Socio demographics	age	in years	O1a, O2d, O2f
			sex	female, male, diverse	O1a, O2d, O2f
			school education	number of school years	O1a, O2d, O2f
			occupational education	unskilled, three-year apprenticeship, technical college degree, university degree	O1a, O2d, O2f
			citizenship	list of 202 countries	O1a, O2d, O2f
			family status	married (living together), married (living apart), single, divorced, widowed	O1a, O1b, O2d, O2f
			family contact	no, yes (parents, siblings, children, other)	O1a, O1b, O2d, O2f
			(un)employment	years of unemployment	O1a, O1b, O2d, O2f
			reason for homelessness	job loss, divorce, debt, mental illness, change of location, detention, rental rate, escape from parental home, lease expired, other	O1a, O1b, O2d, O2f
			source of income	social assistance, basic security, unemployment benefit, pension, newspaper sale, collect bottles, begging, other	O1a, O1b, O2d, O2f
			detention experiences	no, yes	O1a, O1b, O2d, O2f
		Medical history	somatic diseases	3-digit ICD-10-GM code*, date of consultation	O2a, O2d, O2e, O2f
			psychiatric diseases	3-digit ICD-10-GM code* (F00-F99), date of consultation	O2a, O2d, O2e, O2f
			dental health	dental problems, consultation of dentist, date of consultation	O2a, O2d, O2e, O2f
			infectious diseases	hepatitis A, B, C, HIV, sexually transmitted diseases	O2a, O2d, O2e, O2f
			medication	prescribed medication by ATC code**, date of prescription	O2a, O2d, O2e, O2f

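### The plan's rule that collinear indicators are no problem in latent class analysis is wrong as written: it holds only for association that class membership explains

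*Protocol article*

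**What the plan says.** The Statistical analysis section says that "statistical analyses might use finite mixture modelling", particularly latent class analysis, "in order to distinguish different types of social and health conditions". The Abstract describes the same step as something that will be done. A latent variable regression is then planned to find factors associated with worsening health.

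On the indicators, the section states: "By performing latent class analysis collinearity between indicator variables is not a problem", "since these procedures are aimed precisely at such configurations and patterns". It gives the model's assumption as follows: "Latent class analysis explicitly assumes that manifest variables occur in common expressions". It then draws a contrast with exogenous covariates, for which "we aim at testing for collinearity between covariates using the following two different approaches": a correlation matrix with a cut-off of 0.8, and the coefficient of determination of each predictor regressed on the others. No corresponding check is described for the indicators, and independence within class is not mentioned.

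Table 1 lists the variables to be extracted from eight data sources. It does not say which of them would be indicators.

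**The concern.** A latent class model explains association between indicators through class membership. Two indicators may be strongly correlated in the whole sample, but within a class they must be independent. When two indicators partly record the same fact, they stay associated within every class. The model can absorb that leftover association only by adding classes or by bending the existing ones towards the duplicated item.

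The number and content of the classes are the product of this analysis, because they are the types of social and health condition to be reported. A class that exists because one fact was recorded twice would be read as a type of patient, and a regression on class membership would then partly explain a recording pattern. An analyst who follows the sentence as written has no reason to look for this.

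**Working it through.** **The plan's own figure.** The protocol gives no number of classes, selection rule or error rate for this analysis, so there is nothing to reproduce. The check is a simulation.

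**Input from the protocol.** N of about 3000 records (Inclusion and exclusion criteria).

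**Assumed inputs.** Two true classes (40% and 60%); eight binary indicators; item probability 0.70 in one class and 0.20 in the other; number of classes chosen by lowest BIC from models with up to 4 or 5 classes; 20 to 30 runs per setting. In the redundant pair, the second item copies the first with probability κ and is otherwise drawn independently given class.

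**What κ means.** Within a class with item probability a, the covariance of the pair is κ·a(1−a) and each variance is a(1−a), so the within-class correlation is κ.

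**Correlation from class membership alone.** With class share p, item probabilities a and b, and overall prevalence m = pa + (1−p)b:

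r = p(1−p)(a−b)² / [m(1−m)]

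- a = 0.70, b = 0.20: m = 0.40, so r = 0.24 × 0.25 / 0.24 = 0.25.
- a = 0.95, b = 0.05: m = 0.41, so r = 0.24 × 0.81 / 0.2419 = 0.80.

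With copying, the overall correlation is κ + (1−κ) × 0.25.

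**Raw agreement of the pair.** Chance agreement within class is 0.70² + 0.30² = 0.58 and 0.20² + 0.80² = 0.68, on average 0.4 × 0.58 + 0.6 × 0.68 = 0.64. With copying, agreement is κ + (1−κ) × 0.64.

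**Results at N = 3000, true number of classes 2:**

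| Setting | Overall r of pair | Agreement | Classes chosen by BIC |
|---|---|---|---|
| No copying | 0.25 | 64% | 2 in 30/30 |
| No copying, items 0.95/0.05 | 0.80 | – | 2 in 20/20 |
| κ = 0.1 | 0.33 | 68% | 2 in 20/20 |
| κ = 0.2 | 0.40 | 71% | 2 in 15/30, 3 in 15/30 |
| κ = 0.3 | 0.48 | 75% | 3 in 6/20, 4 in 14/20 |
| κ = 0.5 | 0.63 | 82% | 4 in 30/30 |
| κ = 0.8 | 0.85 | 93% | 4 in 30/30 |

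At N = 1000 with one pair, κ = 0.2 gave 2 classes in 20/20, κ = 0.5 gave 3 or 4 in 20/20, and κ = 0.8 gave 4 in 20/20.

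**Forcing two classes does not remove the problem.** At κ = 0.8 and N = 1000, the probability in the high class was estimated at 0.94 for the duplicated item and 0.58 for an ordinary item; both are truly 0.70. At κ = 0.1 and N = 3000 the distortion was negligible (0.71 and 0.70).

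**A subset item.** In a small separate check (N = 3000, two true classes, four runs per setting, up to four classes fitted), an indicator that is merely a subset of another led to 3 or 4 classes in 4/4, against 2 classes in 4/4 without redundancy.

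**Overlap among the candidate variables in Table 1:**
- Detention is one of the reasons for homelessness ("job loss, divorce, debt, mental illness, change of location, detention, rental rate, escape from parental home, lease expired, other") and detention experience is a separate yes/no item. The first implies the second.
- Debt is in the same list of reasons, and "indications of debts" is a separate item in the floating medical record.
- Source of income and status of financial support share four named categories.
- ICD codes are extracted from six of the eight sources (1, 2 and 4 to 7).

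**The case against.** The strongest defence is context. The sentence opens a contrast with regression and can be read as saying only that association among indicators is what latent class analysis models. To that extent it is right: an overall correlation of 0.80 arising purely from class membership produced no extra classes. This stands, and it is why the sentence needs qualifying rather than reversing.

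A reader might infer that the plan asserts the opposite of local independence or forbids residual checks. It does neither; it omits the assumption and directs its checks elsewhere.

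A reader might also infer that Table 1 will produce spurious classes. The document does not support that. Table 1 is an overview of data sources, not a list of indicators. Overlapping sources may be combined when variables are built, and an article commonly leaves such detail to an analysis plan. The absence of an indicator list or merging rule is not the fault here; the stated rule is.

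Several pairs are also not strict duplicates: having debts is not the same as losing housing through debt, and financial support is recorded as a later change whereas source of income comes from the first-visit form. Nothing in the document supports agreement of 90% or more for them. This weakens the case but does not remove it, because extra classes appeared in every run at about 75% agreement, where chance alone gives 64%, and also for a subset item.

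Finally, the study is exploratory, and the Statistical analysis section leaves the mixture modelling optional. That limits the weight of the point, not its correctness.

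**Conclusion.** Wrong as written. Correlation that class membership explains is harmless; association that remains within class is not, and the blanket sentence does not separate the two. Under the assumed settings at N = 3000, one overlapping pair had no effect at 10% copying, produced an extra class in half of runs at 20%, and produced extra classes in all runs from 30%. At N = 1000, 20% copying was still harmless.

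These figures rest on an assumed number of items, class sizes, item probabilities and BIC selection. Whether the study would be affected depends on which variables become indicators and how strongly they remain associated within class, neither of which the protocol gives. The supported conclusion is that overlapping indicators can yield spurious or item-defined classes, not that they will.

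**What to change.** 1. Qualify the sentence: association between indicators is acceptable only where class membership explains it (local independence).
2. State that candidate variables recording the same fact are merged into one indicator before modelling, for example one indicator per condition across data sources and detention once.
3. State that bivariate residuals are inspected in the candidate models, and that items are merged or a direct effect allowed where residuals are large, before the number of classes is fixed.

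Extending the planned 0.8 correlation cut-off to the indicators would not serve. In the simulation it would pass pairs at 0.40 to 0.63 that created extra classes, and flag a pair at 0.80 that did no harm.

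The cost is slightly fewer indicators and a little more model checking. No new data are needed.
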